### Sample size

The sample size was determined on the basis of previous studies conducted to test the efficacy of a vegetarian diet on patients with type 2 diabetes mellitus [12]. To achieve an effect size between 1.25 and 2.1 for a power of 80 % at alpha < 0.05, for two groups, with a mean difference between groups from 2 to 3.5 kg and a standard deviation between 1.6 and 3.9, a sample size of at least 50 in each group of the study was required. It is projected that 100 subjects will be required in the final database and 10–25 % more must be randomized to achieve this number of completed subjects. These projections will be reviewed throughout the course of the study. Losses will be included in the intention-to-treat but not in the per-protocol analyses. The sample size calculation was performed using an online calculator software (available at http://www.powerandsamplesize.com).

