### Statistical analysis

Statistical analyses will be performed using SPSS software for Macintosh (SPSS Inc., Chicago, IL, USA). Outcomes will be analysed by intention-to-treat and on-treatment procedures. Histograms and box plots will be used to assess the distributional assumptions and to check for possible outliers. Log transformations will be applied, where appropriate, in order to render the outcome distributions closer to the normal. Bootstrap techniques will be used if this does not achieve reasonable normality to the extent that it may influence the properties of the regression analysis. Continuous variables that follow an approximately normal distribution will be summarized using the mean and standard deviations. Categorical variables will be presented in terms of frequencies and percentages. Before starting the data analysis, the level, pattern and likely causes of the missingness in the baseline variables and outcomes will be investigated by forming appropriate tables. This information will be used to determine whether the level and type of missing data has the potential to introduce bias into the analysis results or substantially reduce the precision of estimates for the proposed statistical methods.

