All data will be treated as paired samples from a crossover study. The two interventions will be analysed by taking into account both periods in the two groups of subjects at different stages. The primary outcome, total weight change from baseline, will be analysed within each group using paired comparison *t* tests to test whether the changes from baseline to 3 months, from baseline to 6 months and from 3 to 6 months will be statistically significant. The absolute change (mean value at baseline subtracted from the mean value after intervention for each subject) will be estimated with independent *t* sample tests. One-way analysis of variance will be used for testing differences between changes in the vegetarian and Mediterranean intervention diet groups. A linear regression analysis (after checking regression assumptions), adjusting for age, gender, smoking habits and sedentary lifestyle, will be performed in order to compare the effect of the two different treatments. Data for the general linear model for repeated measurements will be reported as geometric means with their standard errors. A significant effect will indicate that the change from baseline to the vegetarian diet phase will be different from the change from baseline to the Mediterranean diet phase. Secondary outcome variables will be analysed similarly.

Multiple strategies will be employed to reduce attrition, including an accurate recruitment, a structured and time-limited protocol, the inclusion of a run-in period, the limitation of the burden and inconvenience of data collection on the participants and the development of a trusting and collaborative relationship between research units and participants. If participants do not attend a scheduled appointment, a maximum of three telephone calls will be made and one email sent prior to withdrawing the participant from the study. If a participant wishes to withdraw from the study intervention, the reason for withdrawal will be documented in the participant records for the subsequent analysis in the interpretation of the results.

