Sensitivity analyses will be undertaken, based on the assumption that missing outcomes are the worst possible, or the best possible, in different randomization groups. If these show that conclusions may differ based on missing values, then supplementary multiple imputation for missing values will be undertaken. These analyses will account for results of any losses to follow-up insofar as they pertain to differences in measured variables (i.e. under the assumption of missing at random).

For questionnaire items related to acceptability, differences between responses during the vegetarian and Mediterranean diet phases will be tested using the Wilcoxon matched-pairs signed ranks test. The independent samples Mann-Whitney U test will be used to compare the diet groups. To test for differences in reported benefits and adverse effects of the diets, the chi-square test for independent samples will compare the two diet groups regarding frequency of changes in reported symptoms from baseline to final time points, and paired-comparison *t* tests will assess within-group changes over time. A *P* value < 0.05 will be considered statistically significant.

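### Losses are promised a place in the intention-to-treat analysis, but the named tests keep only people with the weights they need, imputation is conditional, and an unresolved missed appointment ends follow-up

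*Protocol article*

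**What the plan says.** On analysis sets, the Statistical analysis section states: "Outcomes will be analysed by intention-to-treat and on-treatment procedures". The Sample size section adds: "Losses will be included in the intention-to-treat but not in the per-protocol analyses". It also says "It is projected that 100 subjects will be required in the final database" and that 10–25% "more must be randomized to achieve this number of completed subjects".

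The primary outcome is weight change from baseline. The Statistical analysis section treats all data as paired. It names paired t tests for 0–3, 0–6 and 3–6 months, independent t tests and one-way analysis of variance on changes, an adjusted linear regression, and a general linear model for repeated measurements. The effect of interest is the change on the vegetarian phase against the change on the Mediterranean phase.

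For missing outcomes, the same section plans sensitivity analyses "based on the assumption that missing outcomes are the worst possible, or the best possible, in different randomization groups". If these suggest that conclusions may differ, "then supplementary multiple imputation for missing values will be undertaken", under missing at random.

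For a participant who does not attend an appointment, "a maximum of three telephone calls will be made and one email sent prior to withdrawing the participant from the study". The section on interventions and participant timeline gives two grounds for stopping the intervention or leaving the study: the participant's request, and the investigator's judgement that health would be compromised.

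**The concern.** An intention-to-treat label tells the reader that everyone randomised counts. Here the promise and the named methods part company. None of the listed tests, in its usual form, can use a person who lacks one of the weights it needs, and nothing in the plan puts such a person into the main analysis. What would be reported is a completers' comparison under an intention-to-treat heading.

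If leaving is related to how well a diet works for the person, that comparison can be biased, and the safeguard is weak because it is conditional on an analysis whose decisive value is not given. The contact rule adds to the problem, because people who might have returned for a later weight measurement are withdrawn.

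**Working it through.** **Inputs.** From Sample size: 100 completers, 10–25% more to be randomised, planning difference 2 to 3.5 kg, SD 1.6 to 3.9. From Recruitment and randomization: 1:1 allocation. From the participant timeline: Time 0, 2 and 4 are months 0, 3 and 6; Time 1 and 3 are months 1.5 and 4.5.

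**1. The plan's own figures.** 100 × 1.10 = 110 and 100 × 1.25 = 125 randomised. The abstract speaks of 100 randomised; I use the Sample size section, which is explicit. The 50 per group is not reproduced by the stated ranges: for "for a power of 80 % at alpha < 0.05, for two groups", a two-sided normal-approximation calculation at the four corners gives 4, 11, 20 or 60 per group. That is a separate matter, and nothing below depends on it.

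**2. Share missing.** 10/110 = 9.1%; 25/125 = 20%. If the allowance were meant as a dropout rate, N/(1−d) gives 112 to 134 randomised and 12/112 = 10.7% to 34/134 = 25.4%. The wording favours the first reading.

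**3. Who enters which analysis.**

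| Analysis | Weights needed | Lost before Time 2 | Lost between Time 2 and Time 4 |
|---|---|---|---|
| 0–3 months | Time 0, 2 | out | in |
| 0–6 months | Time 0, 4 | out | out |
| 3–6 months | Time 2, 4 | out | out |
| Within-person diet contrast | Time 0, 2, 4 | out | out |

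Independent t tests, analysis of variance and regression on changes follow the same rows. A classical repeated-measures general linear model also drops incomplete cases.

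**4. How far the best/worst-case result depends on the unstated value.** Assume equal loss share f in both groups and missing values set k SDs from the group mean, in opposite directions. The shift in the group difference is 2 × k × SD × f.

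| f | SD | k = 1 | k = 2 | k = 3 |
|---|---|---|---|---|
| 9.1% | 1.6 | 0.29 kg | 0.58 kg | 0.87 kg |
| 9.1% | 3.9 | 0.71 kg | 1.42 kg | 2.13 kg |
| 20% | 1.6 | 0.64 kg | 1.28 kg | 1.92 kg |
| 20% | 3.9 | 1.56 kg | 3.12 kg | 4.68 kg |

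The shift can lie well below the planning difference of 2–3.5 kg or exceed it.

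**5. Does the trigger always fire?** Take k = 2 against the observed difference d. The pooled variance with imputed values is SD² × [(1−f) + 4f(1−f)], that is 1.24 SD² at 9.1% and 1.44 SD² at 20%. Then z = (d − 4 × SD × f) / √(variance × 2/n), with n = 55 or 62.5 per group.

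| d, SD | z at 9.1% | z at 20% |
|---|---|---|
| 2, 1.6 | 4.17 | 2.10 |
| 3.5, 1.6 | 8.59 | 6.46 |
| 2, 3.9 | 0.70 | −1.34 |
| 3.5, 3.9 | 2.51 | 0.45 |

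Significance (z > 1.96) is kept in 5 of 8 cases and lost in 3. Whether imputation runs therefore depends on the data and on the chosen extreme.

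**6. The contact rule.** It covers any scheduled appointment, so it includes Time 1 and Time 3, which the paired t tests do not use. Non-attendance is not among the two grounds in the participant timeline section, and no further weight measurement after withdrawal is stated.

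**The case against.** The strongest reply is that this is a condensed article and a statistical analysis plan may exist. Fixing an extreme value in kg is routine content for such a plan, so its absence here is not in itself an error. The plan also commits to studying the level, pattern and causes of missingness before analysis, it does foresee imputation, and a mixed model would rest on the same missing-at-random assumption. All of that stands. It does not reconcile the explicit promise about losses with the tests the article names, nor remove the condition it places on imputation. The contact rule is trial conduct, which no analysis plan can repair.

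A reader might infer more than the documents support:

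- That every paired test needs both phases. The 0–3 month test, and comparisons of phase I changes, need phase I only.
- That a best/worst case is meaningless for weight. It is unspecified; an observed extreme or a set number of SDs would make it workable.
- That any extreme would nearly always overturn the result, so the trigger tells nothing. At 2 SD it does so in 3 of 8 planning cases.
- That one missed visit means withdrawal. Up to three calls and one email come first.
- That Time 1 and Time 3 weights are collected and then ignored. The abstract places anthropometry at the start and end of each phase, the methods speak of follow-up visits, and the time points of the repeated-measures model are not listed.
- That people who leave are those losing least weight. This is plausible, but the documents do not show it.

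**Conclusion.** The point holds in a limited form. Followed as written, the plan gives an analysis of people with the needed weights under an intention-to-treat label, while about 9–20% of those randomised lack the final weight (up to about 25% on the other reading of the allowance). The method that would include them is conditional on a best/worst-case analysis whose shift could be anywhere from 0.29 to 4.68 kg at 1–3 SD, a range I assumed because no value is given. The contact rule makes avoidable losses likely and needs reconciling with the stated grounds for withdrawal.

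This rests on losses at the rate the protocol itself allows for, equal loss in both groups for the shift calculation, and the repeated-measures model being the classical one. The direction and size of any bias in the completers' comparison cannot be derived from the documents. The matter should be put right, but it does not by itself invalidate the trial.

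**What to change.** 1. Make the primary intention-to-treat analysis a likelihood-based mixed model with sequence, period and diet, fitted to all observed weights (Time 0, 2 and 4, plus Time 1 and 3 if recorded), keeping participants with only one phase. It is valid under missing at random. Someone with a baseline weight only will add little information, which is why the second change matters. Make any missing-data sensitivity analysis unconditional, with its shift in kg fixed before the data are analysed; its exact form can be left to the statistical analysis plan.
2. Change the contact rule so that an unanswered missed appointment counts as a missed visit only. The participant is still invited to later weight measurements unless consent is withdrawn. Reconcile this with the grounds for withdrawal in the participant timeline section. This concerns the collection of weights only, not whether anyone continues a diet.

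The cost is revised analysis wording, slightly more analysis work, a small amendment to the contact rule and a few more invitations. Enrolment was still under way when the article was submitted, so both changes were feasible then.

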### Recruitment and randomization

Male and female participants will be recruited by trial personnel using advertisements in local media, newspapers, social media, sheets and official websites. They will also recruit from a pre-existing database of participants and from friends or relatives of the hospital and university staff.

After approval and completion of the initial assessment, subjects will be formally entered into the study and randomized with a 1:1 randomization to study arms by a statistician, using a web-based online randomization procedure. Randomization will be stratified by age. The allocation concealment will be ensured using a centralized service, and it will not be possible for the investigators to know the allocation sequence in advance.

### Blinding

In this trial, blinding of participants and dieticians is not possible because of obvious differences between the intervention diets; however, outcome measures in the present study cannot be easily influenced by the observer. In addition, trial personnel who will enrol participants, outcome assessors and data analysts will be blinded to treatment allocation, and an employee outside of the research team will enter data into the computer in separate datasheets. On the other hand, making the trial open rather than blinded may improve recruitment.

### Data collection

Follow-up assessments and data collection will be undertaken at the Unit of Clinical Nutrition of the Careggi University Hospital, Florence, Italy, by trial personnel. All subjects will be examined between 6.30 and 9.30 a.m. after a 12-h fasting period.

#### Adherence and acceptability

In order to assess diet compliance, participants will be contacted at least twice during the study period. A dietician will make unannounced telephone calls to each participant to administer a 24-h diet recall. Adherence to the vegetarian diet will be measured as the absence of meat and fish from the dietary recalls. Participants in the Mediterranean group will be considered adherent if their food records report a great adherence (≥10 points on the 9-item literature-based Adherence Score Tool) to the Mediterranean diet.

At *Time 2* and *Time 4* participants will complete a modified version of the Food Acceptability Questionnaire asking participants to answer questions regarding the feasibility, the acceptability and the satisfaction/dissatisfaction with both diets. This questionnaire also asks respondents to indicate whether they have frequently experienced any of the following perceived benefits or adverse effects during the intervention period: changes in digestion and gastrointestinal function, increased or decreased energy, better or worse sleep than usual and self-perceived quality of life.

#### Anthropometric measurements and body composition

Weight and height will be measured using a stadiometer. Body mass index (BMI) will be calculated as weight (kg)/height (m)^2^. The body composition will be determined with a bioelectrical Body Composition Analyzer device (Tanita, model TBF-410) at baseline and follow-up visits.

#### Blood samples

Blood samples will be collected at the beginning and at the end of each intervention phase. Blood samples will be centrifuged at 3000 rpm for 15 minutes, aliquoted to yield serum, and then stored at –80 °C until analysis. The following biochemical measurements will be evaluated: complete blood count, lipid profile (total cholesterol, LDL cholesterol, HDL cholesterol, triglycerides), glucose profile (fasting glucose, insulin, HbA1c), liver function tests (aspartate aminotransferase, alanine transaminase, gamma-glutamyl transferase, alkaline phosphatase), renal function tests (serum creatinine, urea, uric acid), mineral profile (sodium, potassium, magnesium, calcium), iron metabolism (iron, ferritin), vitamin profile (vitamin B_12_, folic acid), pro-inflammatory and anti-inflammatory profile [hs-CRP (high-sensitivity C-reactive protein), circulating levels of inflammatory cytokines: IL-1ra (interleukin-1ra), IL-1β (interleukin-1 beta), IL-2 (interleukin-2), IL-4 (interleukin-4), IL-6 (interleukin-6), IL-8 (interleukin-8), IL-10 (interleukin-10), IL-12 (interleukin-12), IL-17 (interleukin-17), IL-18 (interleukin-18), TNF-α (tumor necrosis factor alpha), IFN-γ (interferon-gamma), VEGF (vascular endothelial growth factor), MCP-1 (monocyte chemoattractant protein-1), IP-10 (IFN-γ-inducible protein 10)], as well as antioxidant profile (total antioxidant profile, parameters of lipid peroxidation) and parameters related to vascular endothelial function such as circulating endothelial progenitor and circulating endothelial cell count.

#### Stool samples

Stool samples (four or five scoops totalling 4 g) will be collected before and after each intervention phase. Stool sample collection kits, including containers, will be provided for the participants. It is optional for the participants to provide the stool samples, so they can continue participating in the study even if they choose not to provide stool samples.

### Data management

Data will be collected in an electronic database. Identifiable data will not be recorded in the database or other documents, and participants will be identified by a unique trial ID only. Hard copies of data sheets linking the participant identification number to the person’s contact details will be kept securely in a locked filing cabinet in a locked office, accessible only to key research team members. Participant files and other source data (including copies of protocols, questionnaires, original reports of test results, correspondence, records of informed consent and other documents pertaining to the conduct of the study) will be kept for the maximum period of time permitted by the institution.

### Statistical analysis

Statistical analyses will be performed using SPSS software for Macintosh (SPSS Inc., Chicago, IL, USA). Outcomes will be analysed by intention-to-treat and on-treatment procedures. Histograms and box plots will be used to assess the distributional assumptions and to check for possible outliers. Log transformations will be applied, where appropriate, in order to render the outcome distributions closer to the normal. Bootstrap techniques will be used if this does not achieve reasonable normality to the extent that it may influence the properties of the regression analysis. Continuous variables that follow an approximately normal distribution will be summarized using the mean and standard deviations. Categorical variables will be presented in terms of frequencies and percentages. Before starting the data analysis, the level, pattern and likely causes of the missingness in the baseline variables and outcomes will be investigated by forming appropriate tables. This information will be used to determine whether the level and type of missing data has the potential to introduce bias into the analysis results or substantially reduce the precision of estimates for the proposed statistical methods.

All data will be treated as paired samples from a crossover study. The two interventions will be analysed by taking into account both periods in the two groups of subjects at different stages. The primary outcome, total weight change from baseline, will be analysed within each group using paired comparison *t* tests to test whether the changes from baseline to 3 months, from baseline to 6 months and from 3 to 6 months will be statistically significant. The absolute change (mean value at baseline subtracted from the mean value after intervention for each subject) will be estimated with independent *t* sample tests. One-way analysis of variance will be used for testing differences between changes in the vegetarian and Mediterranean intervention diet groups. A linear regression analysis (after checking regression assumptions), adjusting for age, gender, smoking habits and sedentary lifestyle, will be performed in order to compare the effect of the two different treatments. Data for the general linear model for repeated measurements will be reported as geometric means with their standard errors. A significant effect will indicate that the change from baseline to the vegetarian diet phase will be different from the change from baseline to the Mediterranean diet phase. Secondary outcome variables will be analysed similarly.

Multiple strategies will be employed to reduce attrition, including an accurate recruitment, a structured and time-limited protocol, the inclusion of a run-in period, the limitation of the burden and inconvenience of data collection on the participants and the development of a trusting and collaborative relationship between research units and participants. If participants do not attend a scheduled appointment, a maximum of three telephone calls will be made and one email sent prior to withdrawing the participant from the study. If a participant wishes to withdraw from the study intervention, the reason for withdrawal will be documented in the participant records for the subsequent analysis in the interpretation of the results.

Sensitivity analyses will be undertaken, based on the assumption that missing outcomes are the worst possible, or the best possible, in different randomization groups. If these show that conclusions may differ based on missing values, then supplementary multiple imputation for missing values will be undertaken. These analyses will account for results of any losses to follow-up insofar as they pertain to differences in measured variables (i.e. under the assumption of missing at random).

For questionnaire items related to acceptability, differences between responses during the vegetarian and Mediterranean diet phases will be tested using the Wilcoxon matched-pairs signed ranks test. The independent samples Mann-Whitney U test will be used to compare the diet groups. To test for differences in reported benefits and adverse effects of the diets, the chi-square test for independent samples will compare the two diet groups regarding frequency of changes in reported symptoms from baseline to final time points, and paired-comparison *t* tests will assess within-group changes over time. A *P* value < 0.05 will be considered statistically significant.

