## Methods/design

### Study design and setting

The randomized, open, crossover clinical trial will be conducted at the Unit of Clinical Nutrition of the Careggi University Hospital, Florence, Italy. A crossover design will be implemented to allow comparison of the vegetarian and Mediterranean diets within the same individual. Participants will act as their own controls in crossover studies, so individual differences will be controlled for, making the error variance smaller and subsequently reducing the sample size required to find a significant effect due to increased statistical power. This design will also be adopted in an effort to minimize attrition and to maximize participant interest and compliance by enabling each participant to experience both diet conditions. The study design follows the SPIRIT guidelines (see Additional files 1 and 2).

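### The tests named for comparing the diets have no participant, period or sequence term, contradicting the paired crossover analysis the plan announces, and none is designated primary

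*Protocol article*

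**What the plan says.** The section Study design and setting gives the reason for the design: "A crossover design will be implemented to allow comparison of the vegetarian and Mediterranean diets within the same individual". It expects a gain in precision from this: "Participants will act as their own controls in crossover studies, so individual differences will be controlled for, making the error variance smaller".

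The section Statistical analysis opens in the same spirit: "All data will be treated as paired samples from a crossover study", and "The two interventions will be analysed by taking into account both periods in the two groups of subjects at different stages". It then names these analyses for weight change:

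- Paired t tests within each group for 0–3, 0–6 and 3–6 months.
- For the absolute change ("mean value at baseline subtracted from the mean value after intervention for each subject) will be estimated with independent"), t tests for independent samples.
- "One-way analysis of variance will be used for testing differences between changes in the vegetarian and Mediterranean intervention diet groups".
- A linear regression "adjusting for age, gender, smoking habits and sedentary lifestyle, will be performed in order to compare the effect of the two different treatments".
- A repeated-measures model, which appears only in a sentence on reporting: "Data for the general linear model for repeated measurements will be reported as geometric means with their standard errors". The next sentence says that a significant effect will mean the changes on the two diets differ, without saying which model or term is meant.

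Secondary outcomes are to be analysed in the same way, and P < 0.05 is the only significance rule given.

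**The concern.** In a two-period crossover each completer supplies one change on each diet. If the independent t test or one-way ANOVA is run on the changes from both phases, the two sets of values come from the same people but are treated as coming from different people. With two diets, one-way ANOVA is the independent t test. The regression covariates describe the person and are the same in both phases, so they replace neither a participant term nor a period term. The paired t tests do use pairing, but they test change over time, not diet. On two calorie-restricted diets they would be expected to show weight loss whichever diet is better.

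At stake are the error rate and the power of the primary comparison and, through the instruction to treat secondary outcomes similarly, of all the others. If completion differs between the sequences, part of the difference between months 0–3 and months 3–6 would also be counted as a diet effect. Because no test is named as primary, the analysis that decides the trial could be chosen after the data are seen.

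**Working it through.** **Inputs.** From the protocol article: 50 per sequence, so N = 100 people and 200 phase changes; SD 1.6 to 3.9 kg; alpha 0.05, taken as two-sided; 1:1 randomization. The article gives no within-person correlation (ρ) and no period effect (D). Both are assumptions here and are shown as ranges. It states no error rate for these tests, so there is no figure to reproduce.

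**Standard error.** With equal sequences, the variance of the difference between diet means is 2s²(1 − ρ)/N. The independent test estimates it as 2(s² + D²/4)/N. Its test statistic therefore has SD k = √[(1 − ρ)s²/(s² + D²/4)] under no diet effect, and its true type I error is 2Φ(−1.96/k).

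| ρ | D (kg) | k | Type I error |
|---|---|---|---|
| −0.5 | 0 | √1.5 = 1.225 | 11.0% |
| −0.13 | 0 | √1.13 = 1.063 | 6.5% |
| 0 | 0 | 1 | 5.0% |
| +0.5 | 0 | √0.5 = 0.707 | 0.56% |
| +0.5 | 3 (s = 2.75) | √(0.5 × 7.56/9.81) = 0.621 | 0.16% |

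Simulation (4,000 trials per setting, SD 3.9, D = 0) agrees: 12.2% at −0.5, 4.5% at 0 and 0.6% at +0.5.

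**Which correlations are plausible.** If each change is taken from the start of its own phase, the Time 2 weight ends one change and starts the next, so its noise enters with opposite signs. With an assumed 1 kg SD of visit noise and s = 2.75 kg (the midpoint of 1.6 and 3.9), this contributes −1/2.75² = −1/7.56 = −0.13. Reaching −0.5 would require all of the variance in change to be visit noise, that is 2.75/√2 = 1.94 kg per visit. Stable individual response to calorie restriction pushes ρ upward. So does taking both changes from Time 0.

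**Power lost.** For a true difference of 1 kg at SD 3.9 and ρ = +0.5, the true standard error is √(2 × 15.21 × 0.5/100) = 0.39 kg.

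- A crossover analysis has power of about Φ(1/0.39 − 1.96) = Φ(0.60) = 0.73 (simulated 0.72).
- The independent test needs a difference above 1.96 × √(2 × 15.21/100) = 1.08 kg, so its power is about Φ((1 − 1.08)/0.39) = Φ(−0.21) = 0.42 (simulated 0.42).
- With an assumed 4 kg period effect, the independent test falls to 0.28 (simulated) and the period-adjusted one stays at about 0.72.

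**Bias.** With n₁ and n₂ completers in the two sequences, the diet means carry period-1 shares n₁/(n₁ + n₂) and n₂/(n₁ + n₂), so the bias is D(n₁ − n₂)/(n₁ + n₂). With equal sequences it is zero. With 50 versus 40 completers and D = 3 kg it is 3 × 10/90 = 0.33 kg.

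**After the fix.** In every simulated setting (ρ from −0.5 to 0.7, D from 0 to 4 kg, equal and unequal sequences), the period-adjusted within-person analysis held a type I error of 4.4% to 5.6% with bias near zero.

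**The case against.** The best defence is that the plan does not ignore the crossover. It promises to take both periods into account and mentions a repeated-measures model, followed by a sentence that can be read as defining the diet test. With phase within subjects and sequence between subjects, the phase-by-sequence term of such a model is the period-adjusted diet comparison. An article may leave the factors to a fuller document. In addition, the article often uses the word groups for the randomized arms. On that reading an independent test in period 1 is valid, and an independent test of each person's period difference between sequences is a standard crossover test.

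Much of this stands, and it rules out several stronger readings:

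- A reader might infer that pairing and period are absent from the plan. The two sentences just described show otherwise.
- A reader might expect an 11% false-positive rate. That needs ρ = −0.5, which is implausible for fasting morning weights.
- A reader might conclude that the period effect will bias the result. With 1:1 sequences and equal completion it does not.
- A reader might put a figure on the inflation from several competing tests. The article does not define the set of tests well enough for that.
- A reader might fault a paired diet t test that lacks a period term. The plan names no such test.

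The contradiction itself is not removed. The factors of the repeated-measures model are not given, it is not called primary, and the independent tests stand beside it as the stated diet comparison. Nothing restricts them to period 1 or applies them to period differences. Restricting them to period 1 would discard the crossover.

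**Conclusion.** The point holds as a contradiction between the announced paired crossover analysis and the tests named for comparing the diets. If those tests are applied to both phases, their standard error is wrong, and the direction depends on an unknown correlation. With positive correlation they are conservative (type I error about 0.6% at ρ = +0.5, and power for 1 kg of 0.42 against 0.72 at SD 3.9). With mildly negative correlation they are slightly anti-conservative (about 6.5% at −0.13).

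A period effect costs precision when the sequences are equal and causes bias only when completers are unequal. The example of 0.33 kg compares with a planning difference of 2 to 3.5 kg. Unequal completion is possible, since the Sample size section provides for randomizing 10–25% extra to cover losses, but the article gives no reason to expect that losses will differ by sequence.

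All sizes rest on assumed values of ρ, D and completion. The article supports the contradiction and the missing designation of a primary test. It does not support a claim that the trial's result will be biased.

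**What to change.** For the diet comparison, replace the independent t tests, the one-way ANOVA and the separate regression with one pre-specified crossover model for weight change: fixed effects of diet, period and sequence, and a random participant effect (SPSS MIXED). The equivalent repeated-measures GLM, with phase within subjects and sequence between subjects, would also serve. Then:

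- Name the diet effect with its 95% CI as the sole primary test.
- State whether each change is taken from Time 0 or from the start of its own phase. This is a substantive choice, because it decides what the second-phase change measures.
- Treat the within-group changes over time as descriptive, not as evidence of a difference between diets.
- Apply the same model to the secondary outcomes.

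The cost is a revision of the Statistical analysis text and a decision on the baseline. No new data, visits or software are needed.
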